## STEPS FOR ADJUSTING NUTRITIONAL SUPPORT VOLUME AND CALORIES (Figure 2)

1. Subjects will be assessed during weekly telephone visits and at each study visit for hydration and nutrition. A diary will be kept by the caregiver. The caregiver will make all measurements prior and after the scheduled study visits.
2. Nutritional Support changes will be made in accordance with Figure 2. Additional considerations include the following:

- Consideration for nutritional support reduction and advancement of enteral feeds will be in the context of maintaining clinical status and the opportunity to gain additional days off per week of infusions or be completely weaned off nutritional support.
- Reductions in nutritional support will be considered in terms of calories and/or volume per week, hours per day, and complete days off.
- This adjustment will be done under the supervision of and consultation with the investigators.

Figure 2. Nutritional support adjustments based on calories

[figure not shown]

# EXPERIMENTAL PROCEDURES

## OVERVIEW: SCHEDULE OF TIME AND EVENTS

This clinical trial includes an initial screening visit in which subjects will be screened for eligibility. At screening the investigator or designee will explain the purpose and evaluations of the study to the subject’s parent or legal guardian, and obtain informed consent (and assent, if applicable). If consent is given and based on the results of the screening assessments, the subject will be enrolled in the study. Parents or guardians will receive education and support from a study dietician to assist them in keeping track of daily caloric intake and composition (fat, carbohydrates, protein) in oral and enteral feeds, and TPN. As part of this education, the subject’s parent or guardian will receive access to a nutrition/food tracking phone application (Cronometer) to assist them with these tasks throughout the study. A registered nurse will review how to perform accurate stool collection and subjects will be provided with a stool container in the event they are eligible.

If enrolled based on the results of screening, the subject and legal guardian will then be required to perform a 72-hour stool collection and caloric intake recording during the enrollment period (Days -3 to -1) of the study. The subject will return to the clinic on Day 1. At this clinic visit, any baseline assessments not obtained during the enrollment period will be performed, and the first treatment will be administered. Baseline assessments will include physical examination, nutritional assessment, vital signs, clinical evaluations and blood collection for lipid/FA profiles. Physical examinations performed during the 3-day enrollment period will be used for the baseline assessment when available. The subject’s nutritional intake (enteral and oral intake, and PN volume) and stool consistency/amount/frequency (if applicable) or ostomy output (if applicable) will be assessed. At this and each subsequent visit, parents or guardians will continue to receive nutrition education and support from a study dietician.

During the treatment period, all enteral nutrition will be administered using the RELiZORB enzyme cartridge. Nutritional intake and composition (24 hour oral and enteral intake and PN volume) will be recorded on the phone based application (Cronometer; or paper). Stool consistency (assessed through the Bristol scale), stool amount/frequency (if applicable) or ostomy output (if applicable), study device use, and incidence of any changes in symptoms (e.g., abdominal pain, increases in stool output above baseline, change in urine color/frequency) will be recorded by the subject’s parent or guardian in their electronic or paper diary. After the daily phone call with a study coordinator, the coordinator will email the study team list serve to address any issues or concerns as these occur. Advancement of oral or enteral feedings and weaning from PN feeding will be determined by the investigator weekly and at each clinic visit based on the subject’s clinical status, which will include assessment of weight, growth and hydration status. Assessments for the study endpoints and safety will be collected at clinic visits, by physical examination, clinical evaluations and review of the subject’s diary. Assessments will also occur at interim weekly telephone visits after the Day 14 clinic visit as above.

A complete overview of the time and events schedule of this study is presented in Table 2.

Table 2. Schedule of Time and Events

|  | **Study Period** | | | | | | | | |
| --- | --- | --- | --- | --- | --- | --- | --- | --- | --- |
|  |  | | **Treatment Period** | | | | | | |
| **Measurements/Evaluations** | **Screen-**  **ing**  **Day -3** | **Enroll-ment**  **Days**  **-3 to -1** | **Baseline and first treatment**  **Day 1** | **Day**  **2-6** | **Day 7±3** | **Day**  **8-13** | **Day 14±3** | **Day**  **15-27**  **Day**  **29-59**  **Day**  **61-89** | **Day**  **28±3**  **Day**  **60±3**  **Day**  **90±3** |
| I/E criteria | X |  |  |  |  |  |  |  |  |
| Informed consent | X |  |  |  |  |  |  |  |  |
| Demographics | X |  |  |  |  |  |  |  |  |
| Bowel length^a^ | X |  |  |  |  |  |  |  |  |
| Standard of care | X | Daily | X | Daily | X | Daily | X | Daily | X |
| Medical history | X |  |  |  |  |  |  |  |  |
| Vital signs^b^ | X |  | X |  | X |  | X |  | X |
| Anthropometry/Physical exam^c^ | X |  | X |  | X |  | X |  | X |
| Study Coordinator Call |  | Daily |  | Daily |  | Daily |  | Daily |  |
| Clinical laboratory evaluations^d^ | X |  |  |  | X |  | X |  | X |
| Dietician Education | X |  | X |  | X |  | X |  | X |
| 72-hour fecal collection^e^ |  | X |  |  |  |  |  |  | X (final visit) |
| Lipid profile^f^ | X |  |  |  | X |  | X |  | X |
| Total plasma FAs^g^ | X |  |  |  | X |  | X |  | X |
| Liver tests^h^ | X |  |  |  | X |  | X |  | X |
| Nutritional assessment | X |  | X |  | X |  | X | Weekly | X |
| Record nutritional intake^i^ |  | Daily | X | Daily | X | Daily | X | Daily | X |
| Change in PN/ enteral feeding | X | X | X |  | X |  | X | Weekly | X |
| Home Body weight (WAZ) |  |  |  |  |  |  |  | Weekly |  |
| RELiZORB |  |  | X | Daily | X | Daily | X | Daily | X |
| Adverse Events^j^ |  |  | X | Daily | X | Daily | X | Daily | X |
| Concomitant Medications |  |  | X | Daily | X | Daily | X | Daily | X |
| Assess medical/ surgical procedures | X |  | X |  |  |  | X |  | X |
| Supply Investigational Product |  |  | X |  | X |  | X |  | X |
| Review Daily Patient Diary |  |  |  |  | X |  | X | Weekly | X |

I/E criteria = Inclusion and exclusion criteria.

FAs =fatty acids.

PN = Parenteral nutrition.

^a^ Record known bowel length/type from last surgical resection or other measurement.

^b^ Blood pressure, pulse rate, respiratory rate and temperature.

^c^ Includes height or length, head circumference (for subjects < 36 months), and weight. If a physical examination or nutrition assessment was performed during the 3-day screening period, it will be used for the baseline assessment when available.

^d^ Includes chemistry (including fat-soluble Vitamins A, D, E, and K), hematology, coagulation and C-reactive protein (CRP). Clinical laboratory evaluations obtained at time of screening will serve as the baseline assessment.

^e^ 72-hour fecal collection will occur in the 72 hours preceding treatment day 1 and the final clinic visit day 90

^f^ Samples of the lipid profile will include cholesterol, high-density lipoprotein (HDL), very low-density lipoprotein (VLDL), and low-density lipoprotein (LDL). Results of samples obtained at time of screening will be analyzed during enrollment period, prior to participant receiving device.

^g^ Samples of total plasma fatty acids will include total saturated, total monosaturated, total polyunsaturated, total Omega-3, total Omega 6, total fatty acids, a-linolenic Acid, linoleic acid, oleic acid, EPA, arachidonic acid, mead acid, DHA, and triene:tetraene ratio.

^h^ Serum alanine aminotransferase (ALT), serum aspartate aminotransferase (AST), and serum gamma-glutamyl transpeptidase (GGT)

^i^ 24-hour nutritional intake/composition (PO and enteral dietary intake and PN volume) will be recorded using a phone-based application or paper diary. This will be especially important during the 72-hour stool collection periods for calculation of the coefficient of fat absorption.

^j^ Adverse events will be recorded daily in an electronic or paper format by the subject’s parent or guardian, and by study staff during clinic visits. Monitoring of these events will also occur through a daily phone call from a study coordinator. If any AEs or concerns are noted by the family, the study coordinator will alert the study team by email. PI or other delegated investigator will determine next steps

# MEASUREMENTS AND EVALUATIONS

### Screening Period (Day -3)

Before the initiation of screening assessments, the subject and/or subject’s parent/guardian must be given a complete explanation of the purpose and evaluations of the study. Subsequently, the subject and/or subject’s parent or guardian must sign and receive a copy of an informed consent form and an authorization for use and disclosure of protected health information that was approved by the institutional review board or independent ethics committee. Once informed consent and authorization for use and disclosure of protected health information have been obtained, the screening assessments will be performed, and the eligibility of the subject will be determined*.*

The following evaluations will be performed to assess the subject’s eligibility for the study:

- Complete medical history, including bowel length from last surgical resection and any other medical/surgical procedures done.
- Vital signs
  - Temperature, blood pressure, pulse rate, and respiratory rate
- Overview with study participant and parent/guardian of methods of stool collection and storage to ensure compliance
- Clinical lab evaluations including:
  - Chemistry (sodium, potassium, chloride, CO2, glucose, blood urea nitrogen (BUN), creatinine, calcium, phosphorus, magnesium, alkaline phosphatase, albumin, pre-albumin, total protein, total and direct bilirubin
  - Hematology
  - Coagulation
  - Fat-soluble Vitamins A, D, E and K
  - Serum C-reactive protein (CRP), fatty acid profile
- Lipid Profile including:
- Triglycerides, cholesterol, high-density lipoprotein (HDL), very low-density lipoprotein (VLDL), low-density lipoprotein (LDL))
- Total plasma Fatty Acids including:
- Total saturated, total monosaturated, total polyunsaturated, total Omega-3, total Omega 6, total fatty acids, a-linolenic Acid, linoleic acid, oleic acid, EPA, arachidonic acid, mead acid, DHA, and triene:tetraene ratio
- Liver tests including:
- Serum alanine aminotransferase (ALT), Serum aspartate aminotransferase (AST), Serum gamma-glutamyl transpeptidase (GGT)
- Nutritional intake
  - Oral and enteral intake and PN volume intake (total calories and composition in terms of fat, carbohydrate, proteins)
  - Stool consistency (Bristol scale)/amount/frequency (if applicable)
  - Ostomy (if applicable) output

### Enrollment Period (Day -3 to -1)

After completion of screening and if eligible, the subject will be enrolled in the study. During this enrollment period, the subject’s parent or guardian will be responsible for a 72-hour stool collection preceding Day 1. If necessary (for example, out of state participants, excessively watery stools), subjects will be admitted to a dedicated research center at our institution during this collection period. This stool collection will be repeated prior to the final Day of the study (Day 90).

### First Day of Treatment (Day 1)

Baseline evaluations will be performed for assessment of safety and clinical endpoints.

Assessments of safety will include:

- Vital signs
  - Temperature, blood pressure, pulse rate, and respiratory rate
- Physical examination
  - Height or length, head circumference (for subjects < 36 months), and weight.
  - Physical examinations performed during the 3-day screening period will be used for baseline assessment when available

• Concomitant Medications

• Medical/ surgical procedures

**Assessments of clinical endpoints will include:**

- Review of results of 72-hour stool collection that occurred during enrollment period as noted in section 7.1.2:
  - Stool total fat and fatty acid measurements
  - Measurements of dietary (oral/enteral) and PN intake of fat and during the 72-hour collection
- Review of lipid profile results from samples collected at screening visit as noted in section 7.1.1.
  - Cholesterol, high-density lipoprotein (HDL), very low-density lipoprotein (VLDL), low-density lipoprotein (LDL), triglycerides.
  - The lipid profile will be obtained at time of screening but will not be analyzed until patient has been enrolled into the protocol.
- Review of fat-soluble vitamins in plasma samples (Vitamin A, D, E, and K) results from samples collected at screening visit as noted in section 7.1.1.
- Nutritional intake
  - Oral and enteral intake and PN volume intake will be documented in the electronic phone application (Cronometer) or paper diary and will be available to study staff in real time.
  - Stool amount/frequency or ostomy (if applicable) output

On study Day 1, subjects will receive their enteral nutrition through the RELiZORB enzyme cartridge.

The subject’s parent or guardian will be given access to a phone-based nutrition tracking application (Cronometer) for recording nutritional intake (oral and enteral intake and PN volume). The subject’s parent or guardian will also have access to an electronic diary (or paper if no electronic capabilities) and instructed to record any changes in symptoms [e.g., abdominal pain, changes in stool consistency based on the Bristol scale, increases in stool output above baseline, stool amount/frequency (if applicable) or ostomy (if applicable) output, changes in urine color (through dehydration color scale) and frequency and administration of the study device]. The subject’s parent or guardian will be instructed how to store and administer the study device and will be provided with the study device to take home.

The first time the device is used to administer enteral nutrition will be done so under the supervision of a member of the research team; the patient’s response will be monitored at clinic. Investigational product will be supplied at each clinic visit. The feeding regimen, including type of formula, will not be changed for research purposes. Subjects will remain on their current regimen. Additionally, only standard (non-blenderized) formulas will be permitted to be used with the RELiZORB enzyme cartridge. Amino-acid based formulas that are compatible with the RELiZORB enzyme cartridge will be permitted.

### Treatment Period (Day 1 to 90)

During the treatment period (Day 1 to Day 90) the study device will be used daily with the administration of enteral nutrition.

At each visit and during weekly phone calls, the investigator will assess the subject’s nutritional intake, weight, growth and hydration status to determine if, based on their medical judgment, changes to the subject’s nutritional treatment should be made.

The subject’s parent or guardian will record the use of the study device, the subject’s nutritional intake (24 hour oral and enteral intake and PN volume), stool amount/frequency or ostomy (if applicable) output, and any changes in symptoms (e.g., abdominal pain, increases in stool output above baseline using the diary). In addition, if the subject experiences any unexpected physical or medical condition, the subject’s parent or guardian will be directed to call the clinic immediately and report it to the study staff.

Subjects will return to the clinic on Day 7, Day 14, Day 28, Day 60, and Day 90 of the treatment period. Site staff will review the information in the subject diary, review study device compliance, and discuss findings with the subject and subject’s parent or guardian during the visit. A study dietician will visit with the subject and subject’s parent or guardian to review nutrition information and address any issues or concerns.

At each clinic visit, vital signs, physical examination, adverse event assessment, concomitant medication review and review of any medical/ surgical procedures, clinical evaluations and liver enzymes will be performed to assess safety. Blood samples will be collected to analyze lipid profiles. Prior to the final visit, 72-hour fecal samples will be collected to analyze fecal composition. Any AEs that occur will be recorded in the CRF.

A daily study coordinator phone call will be done throughout the study (Day 1 to Day 90). The study dietician and investigators will have telephone contact with families during interim weeks after the day 14 visit. Study staff will monitor safety, diaries, and any changes in nutritional support. If necessary, unscheduled visits can be arranged in place of the telephone contacts.

The investigator will assess the subject’s nutritional treatment, weight, growth and hydration status to determine if, based on their medical judgment, advancement of oral or enteral feeding and weaning from PN should occur. This will occur during study visits as well as through the weekly telephone contact with families. Families will be provided with a standardized weight scale at the time of inclusion of the study for consistent weight measurements.

Any AEs that occur after the start of use of the study device will be recorded according to the procedures in Section 9.0[_RECORDING_ADVERSE_EVENTS](#_RECORDING_ADVERSE_EVENTS). Any significant clinical finding prior to administration of the study device will be included in the subject’s medical history.

### Standard of Care

All subjects will receive standard medical, surgical, and nutritional care during the study. Standard nutritional care will be provided as follows:

- All subjects without existing central venous catheters will undergo placement of these catheters for intravenous fluid management and administration of hypertonic nutrition solutions.
- PN will be increased when oral energy intake declines to less than baseline resting energy requirements for more than 3 days or the patient’s underlying clinical condition is such that PN should be initiated immediately so as to maintain protein stores.
- Maintenance fluid requirements for all subjects will be calculated according to the Holliday-Segar Method, detailed in Table 3.
- Amino acids will be provided according to standard, age-adjusted estimations for subjects receiving parenteral nutrition, detailed in Table 4.
- The nutritional regiment for subjects is provided in Table 5.

Table 3. Daily Fluid Requirements by Body Weight, According to the Holliday-Segar Method

| **Daily Fluid Requirements** | |
| --- | --- |
| **Body weight** | **Maintenance Parenteral Fluid Requirements** |
| 0 to 10kg | 100 mL / kg |
| 10 - 20 kg | 1000 mL + 50 mL / kg over 10 |
| Over 20 kg | 1500 mL + 20 mL / kg over 20 |

Table 4. Daily Caloric and Protein Requirements

| **Daily Caloric and Protein Requirements** | | |
| --- | --- | --- |
| **Age** | **kcal/kg/day** | **Protein g/kg/day** |
| 1 to 7 years | 75 to 90 | 1.5 to 3 |
| 7 to 10 years | 50 to 75 | 1.5 to 3 |
| 11 to 12 years | 50 to 75 | 0.8 to 2.5 |
| 13 to 18 years | 30 to 50 | 0.8 to 2.5 |

Table 5. Nutritional Regimen

| Dietary Component | Dose |
| --- | --- |
| Fat (enteral) | No more than 40% of total calories (PN + EN) |
| Electrolytes | As per clinical needs |
| Vitamins | >3 kg and <11 years of age: 5 ml/day MVI Pediatric^®^  >11 years of age: 1 vial MVI 13 (contains 150ug vitamin K) |
| Trace elements | As per clinical needs |

[**7.1.6**](#_MEASUREMENTS_AND_EVALUATIONS)  **Analysis of fecal fat and fatty acids profiles**

Prior to receiving the study device, a 72-hour stool collection will be obtained during the enrollment period for fecal fat and fatty acid analysis. This process will be repeated prior to the final study visits. Throughout the study, plasma samples will also be collected for fatty acid analysis.

*Protocol:*

1. Collected stool is homogenized, weighed and a representative sample is taken.
2. *Quantitative total fat*: The collected stool sample is sent to BCH central lab for quantitative total fecal fat measurement
   1. The coefficient of fat absorption will be calculated using the total stool mass, total fat analysis, and the following equation:

CFA= [Total Dietary fat (72 hours) – Total Stool Fat (72 hours)] ÷ Total Dietary Fat (72 hours)

1. *Stool and Plasma Fatty acid profile* :

Stool and plasma fatty acid composition will be analyzed at OmegaQuant Analytics by gas chromatography (GC) with flame ionization detection. Stool samples will be weighed into a screw-cap glass vial which contain tritricosanoin as an internal standard (tri-C23:0 TG) (NuCheck Prep, Elysian, MN), homogenized and then extracted with a modified Folch extraction. A portion of the organic layer will be transferred to a screw-cap glass vial and dried in a speed vac. After samples are dried BTM (methanol containing 14% boron trifluoride, toluene, methanol; 35:30:35 v/v/v) (Sigma-Aldrich, St. Louis, MO) is added. The vial is briefly vortexed and heated in a hot bath at 100˚C for 45 minutes. After cooling, hexane (EMD Chemicals, USA) and HPLC grade water is added, the tubes are recapped, vortexed and centrifuged help to separate layers. An aliquot of the hexane layer will be transferred to a GC vial. GC will be carried out using a GC-2010 Gas Chromatograph (Shimadzu Corporation, Columbia, MD) equipped with a SP-2560, 100-m fused silica capillary column (0.25 mm internal diameter, 0.2 um film thickness; Supelco, Bellefonte, PA).

1. Fatty acids are identified by comparison with a standard mixture of fatty acids (GLC OQ-A, NuCheck Prep, Elysian, MN) which was also used to determine individual fatty acid calibration curves. Fatty acid composition is expressed as a percent of total identified fatty acids and concentrations as µg/mg of stool.

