### Inclusion Criteria

To be considered eligible to participate in this study, a subject must meet all the inclusion criteria listed below:

1. Male or female patients, aged 2 years – 18 years, inclusively.
2. Diagnosed with SBS, as determined by medical history and PN dependence (i.e. need for PN for >60 days after intestinal resection or a bowel length <25% of expected).
3. Congenital or acquired gastrointestinal disease requiring surgical intervention that has occurred at least 3 months prior to screening.
4. Patient is on parenteral lipid and at least 30% of daily caloric and fluid intake has been provided by PN for at least 6 months prior to screening.
5. Stable PN nutrition requirement, determined by less than 5% reduction in PN nutrition for at least 1 month prior to screening, or at the discretion of the investigator.
6. The patient has a Central Venous Catheter (CVC) at the time of study inclusion.
7. Screening direct bilirubin that is in the normal range for age or is not determined to be clinically significant by the investigator.
8. The patient has an existing feeding tube, receiving enteral nutrition via an enteral feeding pump at a rate>10ml/hr but <120ml/hr, and is able to tolerate at least 10 ml/kg/day enteral nutrition with which the RELiZORB cartridge can be used.
9. Stable enteral nutrition requirement with no change in formula composition or rate for at least 1 month prior to screening.
10. The patient or a parent or legal guardian of the patient is able to read, understand, and is willing to provide informed consent (or assent, if applicable) for the patient.
11. The patient (if assent is applicable) or a parent or legal guardian is able to understand the requirements of the study and is willing to bring the patient to all clinic visits and complete all study related procedures (as determined by the investigator).
12. A parent or legal guardian is willing to provide written authorization for the use and disclosure of protected health information.

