### Exploratory endpoints

- Change in 72-hour fecal fat composition and coefficient of fat absorption from enrollment, assessed at Days -3 to -1, to Days 87-89.
- Change in plasma serum fatty acid profile, and fat-soluble vitamins (A, D, E, and K) from baseline, assessed at Day 7, 14, 28, 60, and 90.
- Change in height (height-for-age z-score) and head circumference (head-circumference-for-age z-score) [in subjects < 36 months]) from baseline, assessed at Day 7, 14, 28, 60, and 90.
- Change in BMI z-score from baseline, assessed at Day 7, 14, 28, 60 and 90.
- Change in PN volume from baseline, assessed weekly.
- Change in enteral nutrition tolerance (calories and volume) from baseline, assessed weekly.
- Change in oral nutrition tolerance (calories and volume) from baseline, assessed weekly.
- Ability to wean from PN, assessed over the entire course of the study.

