## COMPLIANCE WITH INVESTIGATIONAL PRODUCT

The subject’s parent or guardian will be required to document the subject’s daily nutritional intake (24 hour oral and enteral caloric intake/composition and PN volume) using an electronic phone-based application (Cronometer; or paper diary if there is no electronic capability). The study device use and incidence of any changes in symptoms (e.g., abdominal pain, increases in stool output above baseline) will be recorded using the electronic diary (or paper diary). The subject’s parent or guardian will receive education and continued support from a study dietician to assist them in keeping track of nutritional and total caloric intake, as well as caloric composition in the diary throughout the duration of the study. Access to the electronic nutrition application (Cronometer) will facilitate this recording. The first and final clinic visits will be preceded by a required 72-hour stool collection for fat analysis.

The study staff will review the diaries and question the subject or the subject’s parent or guardian about protocol compliance at the clinic and weekly telephone visits. For hospitalized subjects, compliance will be assessed through daily monitoring of nutritional markers and review of medication administration records which utilize point of care bar code technology. Details of the study device use will be recorded on the CRF.

In the event that an out-of-state study patient is hospitalized at a hospital other than Boston Children’s and to ensure patients are able to remain in the study at an outside institution, at the time the patients are enrolled in the study, they will be provided a copy of their signed consent and the study protocol with study team contact information with instructions to bring these materials, along with the supply of RELiZORB devices, to the hospital so that they can use them in the event of an inpatient admission.

If a subject fails to comply with protocol requirements, the subject may be discontinued from the study. Compliance will be considered to have been achieved if the subject receives ≥80% of the planned enteral nutrition using the device.

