# MANAGEMENT OF NUTRITIONAL SUPPORT DURING THE STUDY

Clinical parameters for management of pediatric short bowel syndrome will be considered for advancing nutritional support (PN/IV and/or oral/enteral feeding) in volume and calories during the 90 day study. Adjustment of nutritional support in volume and calories will be made at all planned study visits and during weekly phone calls as deemed appropriate (Figure 2). Clinical parameters to be considered include the following:

- Maintaining growth (including weight and height) by the subjects trending along their growth chart and adjusting calories/volumes to maintain the trend
- Serum electrolytes (assessed during study visits and, if needed for PN adjustment, will also be assessed in between visits)
- Increase in the Volume Intake/Output ratio, including mixed output that can be collected
- Consideration of clinical deterioration in SBS
- Weight loss
- Diarrhea (> 50 mL/kg/day with ostomy)
- Vomiting frequency
- Fluid balance
- Skin breakdown of perianal area

Adjustments will be based on the actual nutritional support in volume and calories the subject infuses. Subjects are expected to remain compliant with the nutritional support prescription in volume and calories during the study. Nutritional support constituents may be adjusted at the discretion of the investigator. During the 48-hour Intake/Output measurement period, no significant changes to nutritional support will be made. If there is a change in oral fluid intake, the investigator will consider this when adjusting the nutritional support in volume and calories.

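### Section 7.1.5 requires a PN increase on oral energy intake alone, so in this tube-fed population a shift of calories from mouth to tube can raise the primary endpoint with combined intake unchanged.

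*Protocol*

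**What the plan says.** Section 7.1.5 (Standard of Care) sets this rule: "PN will be increased when oral energy intake declines to less than baseline resting energy requirements for more than 3 days". The sentence goes on, after an *or*, to a second ground based on the child's clinical condition. The oral trigger is therefore sufficient alone, and its verb is mandatory.

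The rest of the protocol describes a population fed by three routes:

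- Section 3.2.1 requires a feeding tube and pump, and a child who "is able to tolerate at least 10 ml/kg/day enteral nutrition with which the RELiZORB cartridge can be used". It also requires that "at least 30% of daily caloric and fluid intake has been provided by PN for at least 6 months prior to screening".
- Section 3.3.1 makes change in PN calories the primary endpoint.
- Section 3.3.4 lists "Change in enteral nutrition tolerance (calories and volume) from baseline, assessed weekly" as one exploratory endpoint and gives oral tolerance a separate one.
- Section 7.1.4 has the investigator judge at visits and weekly calls whether "advancement of oral or enteral feeding and weaning from PN should occur".
- Section 5.0 concerns "advancing nutritional support (PN/IV and/or oral/enteral feeding) in volume and calories during the 90 day study", and Section 5.1 sends nutritional support changes to Figure 2, under the investigators' supervision.

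**The concern.** The trigger measures one of two non-parenteral routes and omits the one that the trial works through. Elsewhere the protocol names both routes when it means both: Section 5.0 does so in the words quoted above, and Section 7.1.3 has "Measurements of dietary (oral/enteral) and PN intake of fat". With oral and enteral calories as separate endpoints, a reader has no textual ground for counting tube calories in the Section 7.1.5 trigger.

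Advancing tube feeds is an expected step during the 90 days. A child may eat less by mouth as tube volume goes up. If oral energy then drops below resting requirement for more than 3 days, the sentence orders more PN although combined intake has not fallen. PN calories are the primary endpoint and the study has no control arm, so that increase would be recorded as a worse outcome caused by the care rule and not by poorer absorption.

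**Working it through.** **1. The plan's own precision figures.** Inputs from Section 10.2.5: n = 32, mean AUC_7-90 0.80, SD 0.14 or 0.28. The half-width is t(31) × SD/√32, with t(31) = 2.0395.

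- SD 0.14: 2.0395 × 0.14/5.657 = 0.0505, interval 0.750 to 0.850. The plan gives 0.75 to 0.85.
- SD 0.28: 2.0395 × 0.28/5.657 = 0.1010, interval 0.699 to 0.901. The plan gives 0.7 to 0.9.

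Both reproduce and serve as the yardstick below.

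**2. Which children the trigger can reach.** Oral intake can decline through the resting requirement R only if it starts at or above R. The protocol gives no value for R. Assume that total intake equals the Table 4 need, PN is at the 30% entry minimum, and tube feeding is at the 10 ml/kg/day minimum with 1.0 kcal/mL formula (the lowest density in Table 1). Then the most a child can take by mouth at entry is 0.70 × need − 10 kcal/kg/day.

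| Age band (Table 4) | Need, kcal/kg/day | Oral ceiling, kcal/kg/day | Share of need |
|---|---|---|---|
| 1 to 7 | 75 to 90 | 42.5 to 53 | 57% to 59% |
| 7 to 12 | 50 to 75 | 25 to 42.5 | 50% to 57% |
| 13 to 18 | 30 to 50 | 11 to 25 | 37% to 50% |

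A larger PN share or a denser formula lowers these ceilings. At need 80 the ceiling is 46 (57.5%). With 2.0 kcal/mL formula it is 56 − 20 = 36 (45%). With PN at 50% and 1.0 kcal/mL it is 40 − 10 = 30 (37.5%). Where R lies above the ceiling, oral intake cannot decline through it and the oral trigger does not fire.

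**3. A worked case (assumed values, kcal/kg/day).** Need 80, PN 0.30 × 80 = 24.

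| | Oral | Tube | Oral + tube |
|---|---|---|---|
| Before | 44 | 12 | 56 |
| After | 36 | 20 | 56 |

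The rule as written fires if 36 < R ≤ 44, that is, R above 45% and up to 55% of need. A rule on combined intake does not fire, because 56 exceeds every R in that range.

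**4. Effect on the endpoint.** Section 10.2.2 defines AUC_7-90 as a trapezoid time-weighted average of the ratio to baseline over 83 days (Days 7, 14, …, 84, 90), where 1 means no change. Take a 10% PN rise in one child who is otherwise unchanged:

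- Seen at Day 28 only: 0.5 × 14 × 0.1/83 = 0.7/83 = 0.0084 for that child; divided by 32, 0.0003 on the mean.
- Held from Day 28 to Day 90: (0.5 × 7 × 0.1 + 62 × 0.1)/83 = 6.55/83 = 0.079 for that child; divided by 32, 0.0025 on the mean.

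The larger value is 0.00247/0.0505 = 4.9% of the half-width at SD 0.14, and 0.00247/0.1010 = 2.4% at SD 0.28.

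**5. A harsher set of assumptions.** Suppose 3 of 32 children each move 5% to 10% of total energy from mouth to tube, and PN is raised by the same energy from Day 28. With PN at 50% to 30% of energy at baseline, the PN ratio becomes 1.10 (0.05/0.50) to 1.33 (0.10/0.30), and each child's AUC_7-90 becomes 1.079 to 1.263. The mean moves by 3/32 × 0.079 = 0.007 to 3/32 × 0.263 = 0.025. That is about 15% to 49% of the half-width at SD 0.14. Nothing in the protocol supports three affected children or calorie-for-calorie PN increases, so the gap between steps 4 and 5 reflects only the assumptions.

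**The case against.** The best case for the plan is that Section 7.1.5 is not the operative rule. Section 5.1 sends changes to Figure 2 under investigator supervision. Sections 5.0 and 7.1.4 rest adjustments on growth, hydration, fluid balance and medical judgement. Section 7.1.5 reads like general standard-of-care text: it provides for catheter placement although Section 3.2.1 already requires a central venous catheter, and it speaks of starting PN in children who are all on PN. The word *oral* may be loose wording for any non-parenteral intake, since the protocol's terms for intake vary. The scenario is also narrow, and a needless PN increase would have to survive weekly review.

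Most of this stands, and it limits the consequence. It does not repair the sentence. No visible text counts tube calories in the trigger or says that Section 5 overrides it.

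Three stronger readings are tempting and are not supported:

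- *The rule contradicts Figure 2.* The figure is not visible, so no conflict can be shown. The absence of this trigger from the visible text of Section 5 carries little weight for the same reason.
- *The primary result is materially biased, or efficacy could be falsely shown.* The direction is PN up, which works against the device. The size depends wholly on assumed inputs.
- *Many children meet the trigger from the start.* The sentence speaks of a decline. A child whose oral intake is already below R at entry does not decline through it, and the ceilings in the working suggest that this may be common.

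**Conclusion.** Wrong as written, and minor. Section 7.1.5 fixes a mandatory PN increase on oral energy alone. In a trial where every child is tube-fed, that orders the wrong action when calories move from mouth to tube with combined intake unchanged.

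The effect on the primary endpoint is probably very small: 0.0003 to 0.0025 on the mean AUC_7-90 for a 10% PN rise in one child. It runs against the device and leaves the sample size untouched. These numbers illustrate assumed values and do not estimate what will happen, because the protocol gives no resting requirement and no trigger frequency. Section 5, Figure 2 and investigator judgement may prevent the increase altogether.

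**What to change.** In Section 7.1.5, replace *oral energy intake* with *combined oral plus enteral energy intake*. Do not delete the trigger: it protects a child whose non-parenteral intake really falls. A further cross-reference to Section 5 is optional, since Section 5.1 already sends nutritional support changes to Figure 2.

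The cost is one change of wording in one sentence. It needs no new assessment, visit or patient, because Section 4.4 already requires the family to record "daily nutritional intake (24 hour oral and enteral caloric intake/composition and PN volume" each day.
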